**Preliminary studies:**

***Differences in metabolic response of African Americans and Caucasians to RYGB:* We recently** Caucasianand African American patients who underwent RYGB and analyzed body weight loss over a 24-month period. Data from 16 African American adults were compared to those for a similar group of gender and BMI-matched Caucasians. In preliminary studies**,** we found that the degree of body weight loss after bariatric surgery was significantly lower in African Americans as compared to Caucasians. African Americans lost 40±2.4 lb compared to 61±3.0 lb (p<0.0002) for Caucasian adults**.** Furthermore in another subgroup of patients (n=45) for whom blood samples were obtained immediately preoperatively (176±4 mg/dl, no difference between the two groups) and at day 10 post-operatively, we found that African American patients had significantly (p<0.005) higher fasting plasma glucose levels (135±3 mg/dl) than their white (101±2 mg/dl) counterparts matched for gender and BMI.

These findings demonstrate different metabolic responses of African Americans as compared to Caucasians to RYGB. The mechanisms underlying these differences are completely unknown and exploring them will constitute a main goal of this proposal..The work should contribute insight into some of the reasons behind differences in susceptibility to metabolic pathology. In addition, determining the earliest changes in metabolic regulators and in metabolic symptoms during the postoperative period will provide clues regarding the key determinants behind the metabolic improvements.  ***Body mass index correlates with IsoP levels in vivo:*** Our collaborator, [name] (Chief, Division of Clinical Pharmacology)and his group havecarried out two separate studies showing that BMI was a major determinant of IsoP formation in humans. In the first, they determined factors associated with oxidant stress in a cohort of 298 healthy adults. Amongst a number of parameters the correlation was noted between IsoP was BMI and this association was independent of other risk factors for atherosclerosis. In a second, larger study by [name] *(2002)* involving over 2,800 persons enrolled in the Framingham study, a similar strong association between BMI and IsoP was found. These studies provide compelling evidence that the overweight/obese population has up-regulated inflammatory responses and is under increased oxidative stress. We propose that this is even more pronounced in African American subjects.

***Role of RYGB in reversing T2DM in morbidly obese subjects:***Work performed by [name] recently followed 50 patients with T2DM before and after laparoscopic gastric bypass surgery. The aim of our prospective study was to analyze the efficacy of the procedure in reversing T2DM over a 6-month period. Gastric bypass normalized HbA1C levels and resulted in decreased fasting plasma glucose (p<0.00, for both). Complete resolution of T2DM, defined by normal levels of fasting plasma glucose and HbA1C after discontinuing medical treatment, was achieved in 70% of patients with T2DM. The rest of the patients showed partial responses determined by significant decrements in daily medications.

Multivariate analysis was then used to identify preoperative variables unfavorable for complete resolution of T2DM. The predictive value of each variable in relation to response type (full or partial) was expressed in odds ratio (OR), p value and confidence interval (CI) of 95% of OR. Univariate analysis revealed that (a) treatment with insulin, (b) waist circumference > 50 inches, and (c) levels of HbA1C≥ 8.0% were all associated (p<0.01) with partial responses. To eliminate the effect of confounding factors, we performed a multivariate analysis of the selected variables. The logistic regression model showed that the use of insulin and waist circumference greater than 50 inches remained statistically significant allowing the elaboration of a regression model to predict a full or partial response.

The analysis showed that patients with significant central obesity (waist circumference > 50 inches) when given insulin treatment are less likely to exhibit complete resolution of T2DM after gastric bypass surgery.

| **TABLE 1** | | |
| --- | --- | --- |
| **Variables** | **Baseline** | **6 Months** |
| **Fasting Plasma Glucose *(mg/dL)*** | 161±50 | 108±33 |
| **HbA1C *(%)*** | 7.5 ± 1.6 | 6.2 ± 1.2 |

| **TABLE 2** | | | | |
| --- | --- | --- | --- | --- |
| **Variables** | **χ2** | **P value** | **OR** | **95% CI** |
| **Age** | 2.9 | 0.085 | 0.930 | 0.85-1.01 |
| **Gender** | 0.07 | 0.81 | 0.83 | 0.2-3.9 |
| **Preop Insulin** | 9.4 | 0.002 | 9 | 2.2-36.5 |
| **Waist > 50 inches** | 11.2 | 0.001 | 40.4 | 4.6-352 |
| **BMI** | 3.2 | 0.074 | 1.08 | 0.99-1.2 |
| **Preop oral hypoglycemics** | 2.9 | 0.084 | 1.98 | 0.91-4.3 |
| **HbA1c > 8.0%** | 5.9 | 0.01 | 5.1 | 1.4-18.5 |

***Role of the omentum in modulating insulin sensitivity:*** In an attempt to determine the mechanism by which omentectomy could influence insulin sensitivity *in vivo*, we resorted to the chronically catheterized conscious dog model that we have used extensively in our metabolic studies for the past 2½ decades. This model has the advantage of examining the relative contribution of the liver and peripheral tissue (mostly skeletal muscle) to glucose (and amino acid and FFA) mediated insulin sensitivity in a conscious un-sedated state *(Williams 1990)*. We have thus far finished in five dogs using sequential hyperinsulinemic euglycemic clamps conducted during pre-omentectomy versus post-omentectomy periods separated by a minimum of four weeks recovery. T**T**he amount of omental (+ visceral) fat removed averaged 550 grams.

**4.0 Inclusion/Exclusion Criteria**

**List the criteria:**

***Eligibility criteria for those having bariatric surgery*** include:

- Ages between 18-65
- Serum creatinine 1.5 mg/dL or lower
- Stable body weights for the past three months prior to their approval for the operation

***Exclusion criteria for those having bariatric surgery*** include:

- Significant hepatic enzyme elevations (more than 2 times the upper limits of normal)
- Serum creatinine >1.5 mg/dl and liver function tests greater than 2 times the upper limits of normal
- History of ketoacidosis or current metabolic acidosis
- Positive pregnancy test (β-human chorionic gonadotrophin) for females
- Intercurrent infections
- Taking drugs that are known to affect carbohydrate or lipid metabolism (e.g. steroids, high dose Niacin, β-adrenergic receptor agonists, but does not include antidiabetic drugs)
- Patients with previous bariatric surgical procedures

***Eligibility criteria for normal-weight subjects include:***

- Ages between 18-65 yrs
- BMI 22-27

***Exclusion criteria for normal-weight subjects include*:**

- Significant hepatic enzyme elevations (more than 2 times the upper limits of normal)
- Serum creatinine >1.5 mg/dl and liver function tests greater than 2 times the upper limits of normal
- History of ketoacidosis or current metabolic acidosis
- Positive urine pregnancy test for women in child bearing age.

**Enrollment/Randomization**

**List the process for randomization and/or registration; list the address, phone number or website where the registration will take place.**

***Enrollment for morbidly obese patients*:**

- Patients approved for RYGB, VSG, or AGB are reported to study coordinator
- Coordinator or study nurse screen subjects via Star Panel to determine eligibility

Subjects determined to be good candidates for the study are contacted and the study is described to them. If they show interest, detailed information, including the consent form, is sent to them to read over. The coordinator follows up to respond to questions or concerns.

***Normal Weight subjects who serve as controls:***

**Pre-study:**

- Surgery schedule is sent to study coordinator. Subjects are screened via Star Panel to determine potential candidates. Surgeon is contacted to confirm subjects are suitable.

**Day of Surgery:**

- Subject is met in pre-op area and told about study. Subject is asked if he/she would be willing to let surgeon take muscle and fat samples during the operation. If subject agrees, he/she is consented and surgeon is notified.

**Randomization:** The randomization schedule will be generated by statistical software. The randomization code will be generated using a permuted block size of four. No other restrictions will be used. As each subject is recruited, the randomization is assigned by the coordinator and the surgeon is notified. The PI, [name], will not be involved in the selection and allocation of patients. All recruited patients and researchers involved in the evaluation of the end-points will be blinded to the treatment assigned throughout the whole study period. No interim analyses will be carried out during the course of this study.

1. **Study Procedures**

**Provide a description of what the participants will experience. For example, a description of the instructions that will be given to the participants, activities in which they will engage, the length and timing of involvement, and the circumstances under which they will provide data (e.g., phone calls, spending time in an uncomfortable position, group assessments, one-on-one interview, videotaping, audiotaping, etc.)**

***Subjects who participate in metabolic chamber (the subjects will be assigned to the metabolic chamber in the preoperative period and will have chamber studies again at 6-, 12-, and 24-months post-operatively, as well as 3, 4, and/or 5 years post-operatively, unless otherwise noted):***

**Study Day 0:** Subject reports to the GCRC in the afternoon. The following are performed:

- Measurements of Height, Weight, and Body Circumferences.
- History and Physical Examination
- Performance of EKG (if over age 40)
- Performance of serum pregnancy test (if fertile female)
- Answer SF-36 Questionnaire
- Orders will be written for no food and caffeine after 20:00. They will be made completely NPO after 24:00

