**Study Day 1: The following tests will be performed:**

- DEXA (except 1-month post op)
- IV placed and labs drawn (blood for serum potassium, and for complete blood count, hematocrit, liver function tests, HGB A1c, homocysteine)
- Subject will be escorted to metabolic chamber for 24 hour stay. Collection of 24-hour urine will also begin.
- Blood samples taken hourly from 0730 to 2030 to measure various plasma factors associated with obesity.

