**Study Day 2:**

- Subject escorted from chamber to study room
- IVs placed
- Euglycemic-hyperinsulinemic clamp is begun
- Stable isotope tracer studies for amino acid and fat kinetics begun
- Muscle/fat biopsies are performed about 1 hour after study begins
- Prior to basal sampling period and prior to high-insulin sampling period, subject will be placed on metabolic cart for ½ hour of breathing testing
- Subjects will be given activity monitors to wear for the week after the study (one on wrist and one on waist) along with SASE to mail them back
- At end of study, subject is fed and monitored for at least an hour to assure blood glucose stability

**Subject will have operation, with or without omentectomy, then repeat the above procedures 1-, 6-, 12, and 24-months later. Subjects may also be asked to repeat these procedures at 3, 4, and 5 years post-operatively.**

***Subjects who DO NOT participate in the metabolic chamber (the following procedures will be performed in the preoperative period and at 1-, 6-, 12-, and 24-months post-operatively, as well as 3, 4, and/or 5 years post-operatively, unless otherwise noted):***

**Pre-study and Study Day 0 are the same, except subject is requested to collect 24 hour urine at home and bring the bottle(s) with them when they check into the GCRC.**

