***Statistical Methods, Sample Size, and Power Estimates:*** We based sample size estimates on historical case volumes (>600 procedures per year), patient demographic distributions (70% Caucasian, 25% African American, 5% Hispanic, 80% female 20% male). Persons who consent to participate will be enrolled in both the short and long term phases of the study. We assumed attrition for the short-term phase, which entails data points through postoperative week four, to be negligible, and for the long-term study, which entails a two-year postoperative follow-up period, to be ~ 25% by postoperative month 24. We based this rate on reported attrition following bariatric surgery over a comparable time, and the rate is assumed to be comparable between experimental groups. Anticipated effect sizes were based on previous research or standard conventions for large, medium, and small effects *(Cohen 1988)*. Unless noted, power estimates were determined using standard methods and software (Power and Precision™ v. 2.0, nQuery Advisor™ v. 3.0) for non-directional tests at the 0.05 alpha level.

Demographic information such as age, race, and gender will be tabulated. Descriptive statistics, including means, standard deviations, and ranges for continuous measures, as well as percentages and frequencies for categorical measures will be presented. Statistical analyses will be performed using standard packages (SPSS or SAS).

**Specific Aim 1:** The short-term phase of the investigation will include a group of 66 Caucasians and group of 66 African Americans and Hispanics (each of the two groups randomized to 33 bariatric surgery and 33 bariatric surgery + omentectomy). The long-term phase of the investigation will include at least 100 patients (25 in each of the four racial and procedure groups).

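### The arm is assigned and the surgeon told at recruitment, so on the natural reading both coordinator and surgeon know it while a patient may still drop out before the operation

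*Protocol*

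**What the plan says.** All references are to the protocol.

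- **Time of assignment.** The Randomization paragraph of the Enrollment/Randomization section: "As each subject is recruited, the randomization is assigned by the coordinator and the surgeon is notified". Recruitment is the only time point given, and the term is not defined. The same paragraph keeps the principal investigator out of selection and allocation, and says that patients and the researchers assessing end-points stay blinded throughout.
- **Screening.** The enrolment steps for morbidly obese patients begin with people already approved for a bariatric procedure: "Coordinator or study nurse screen subjects via Star Panel to determine eligibility". Contact, the consent form and the coordinator's follow-up come next.
- **Exclusions.** Section 4.0 lists "Positive pregnancy test (β-human chorionic gonadotrophin) for females" and "Significant hepatic enzyme elevations (more than 2 times the upper limits of normal".
- **Preoperative studies.** Study Day 0 includes "Performance of serum pregnancy test (if fertile female". Study Day 1 includes "IV placed and labs drawn (blood for serum potassium, and for complete blood count, hematocrit, liver function tests, HGB A1c, homocysteine". DEXA, the clamp and the biopsies belong to the same preoperative stay. Patients outside the metabolic chamber follow a shortened version, with laboratory tests and clamp on one day.
- **Operation.** It follows these studies: "Subject will have operation, with or without omentectomy, then repeat the above procedures 1-, 6-, 12, and 24-months later".
- **Attrition.** Statistical Considerations takes short-term loss, "which entails data points through postoperative week four, to be negligible".

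**The concern.** The two arms receive identical care until the patient is in theatre. An assignment made at recruitment therefore opens an interval in which the arm is known to two people but has no use. In that interval a patient may change their mind, decline the clamp, develop an infection, have a positive pregnancy test or raised liver enzymes, or have the operation cancelled. Each such patient has already been randomised.

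Two things are at stake. The first is precision: these patients supply no postoperative values, and analysis by assigned arm cannot create them. The second is comparability. The coordinator screens and follows up candidates and also assigns the arm. The surgeon operates under a protocol that allows three bariatric procedures in both arms and restricts randomisation only by block size. If either lets the known arm influence who proceeds, who is postponed or which procedure is done, the operated groups are no longer purely the product of chance. The protocol has no rule for a patient who is assigned and then not operated on.

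**Working it through.** **Step 1: order of events.** Set side by side, the sections give: record screen, contact and consent material, recruitment with assignment and notice to the surgeon, Day 0 to Day 2 studies, operation. The place of assignment in this chain is inferred from the wording and the order of the sections. No sentence states that assignment precedes Day 0, and none prevents it.

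**Step 2: who knows the arm in the interval.** Only the coordinator and the surgeon are stated to know it. The blinding sentence covers patients and end-point evaluators. No section says that the coordinator or surgeon measures baseline.

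**Step 3: reproduce the plan's power.** Inputs from Statistical Considerations: two-sided alpha 0.05; 33 per race-by-procedure group in the short term (132 in all); d=0.70 with 80% power for one procedure or race comparison within a stratum; d=0.81 with 90% for the Aim 3 comparison; f=0.30 with 92% for overall effects.

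- Two groups of n: noncentral t with 2n-2 degrees of freedom and noncentrality d x sqrt(n/2). For n=33 and d=0.70 this is 0.70 x sqrt(16.5) = 2.84, giving 79.97% (stated 80%). For d=0.81 it gives 89.98% (stated 90%).
- Overall effects: noncentral F with 1 and N-4 degrees of freedom and noncentrality N x f². For N=132 this is 132 x 0.09 = 11.88, giving 92.8% (stated 92%).

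The stated figures reproduce with 33 analysed per group, so they contain no allowance for loss between assignment and surgery. The 25% long-term allowance is also fully used: 132 x 0.75 = 99, against the stated 100.

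**Step 4: effect of loss before surgery.** The protocol gives no rate. The 5-15% range is an assumption, and 132 is taken as the number randomised.

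| Assumed loss | Patients lost of 132 | Per group, 33 x (1 - loss) | Power, d=0.70 | Power, d=0.81 | Power, f=0.30 |
|---|---|---|---|---|---|
| 0% | 0 | 33 | 80% | 90% | 93% |
| 5% | 6.6 | about 31 | 77% | 88% | 91% |
| 10% | 13.2 | about 30 | 76% | 87% | 90% |
| 15% | 19.8 | about 28 | 73% | 85% | 88% |

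**Step 5: numbers needed.** To keep 33 operated patients per group, 33/(1 - loss) must enter: 35, 37 or 39 at 5%, 10% or 15%. This holds whenever assignment is made. Later assignment does not reduce the number recruited; it turns these patients from randomised losses into screening failures.

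**Step 6: sensitivity to the planned total.** The Study Plan under Rationale and Specific Aims gives 150 per arm, or 75 per race-by-procedure group. A 15% loss would then leave 75 x 0.85 = about 64 per group, well above 33, and the power loss in Step 4 would not arise.

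**The case against.** Several stronger readings are tempting, and the protocol does not support them.

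- **That baseline measurement is unprotected from knowledge of the arm.** The Randomization paragraph blinds patients and end-point evaluators for the whole study, and most baseline measures are instrumental or laboratory based. This objection stands in full. The exposure is to decisions about who proceeds.
- **That the Day 0 and Day 1 tests are the eligibility gate.** The protocol places the eligibility screen in the medical record, before contact. The Day 0 and Day 1 items are largely the set repeated at later visits, and the Day 1 list does not name creatinine although creatinine is an eligibility criterion. So these tests cannot be called the deciding ones. They can still reveal an exclusion that arose after the record screen, and there is no rule for that case.
- **That early assignment is proven.** The word for recruitment is undefined, so the order is an inference. That lowers confidence, but it is also a reason to fix the wording, since assignment at consent is permitted as the text stands.
- **That loss in this interval is biased.** A blinded patient's positive test or refusal of the clamp cannot depend on the assignment. Bias requires the coordinator or surgeon to act on what they know. Procedure approval before referral to the study also limits the scope for changing the operation, although nothing locks that choice before assignment.
- **That the attrition assumption is contradicted.** The negligible-loss statement concerns data points through week four and does not clearly cover cancelled operations. The power figures rest on an assumed rate and on 132 randomised, and the larger total in the Study Plan would absorb the loss. Extra numbers would not, however, remove any selective loss.

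**Conclusion.** The point holds in limited form. The protocol does not tie randomisation to confirmed eligibility and completed baseline, discloses the arm to the coordinator and surgeon earlier than any described procedure requires, and has no rule for patients assigned but not operated on. Losses unrelated to the arm are a modest matter of precision: power for d=0.70 goes from 80% to about 77-73%, and for d=0.81 from 90% to about 88-85%, under an assumed 5-15% loss with 132 randomised. If the 300 in the Study Plan are enrolled, that cost disappears. Selective loss is the better reason to act. Its size cannot be estimated from the protocol, and nothing shows that it will occur. The conclusion rests on the natural reading of an undefined term. The change is worth making because it is cheap and protects the randomised comparison.

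**What to change.** Replace the sentence on assignment in the Randomization paragraph with wording such as:

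*Randomisation takes place only after consent, confirmation of all eligibility criteria and completion of the preoperative baseline studies, as close to surgery as practical and after the planned bariatric procedure has been recorded. The surgeon is told the assignment only then.*

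Add two accounting rules. Patients lost before that point are reported as screening failures. Any patient randomised but not operated on stays in the accounting under the assigned arm, with the reason recorded.

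The cost is a short protocol amendment. No visits or staff are added, and the number to be recruited for 33 operated patients per group is the same under either timing. The small downside is that theatre time is booked without knowing whether omentectomy will be added.

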The degree of metabolic improvement following bariatric surgery varies greatly among individuals. The underlying mechanisms behind the improvements and the reasons for individual differences in their onset and magnitude are not well understood. Our preliminary data suggest that the improvements in weight loss and blood glucose after the operation are (a) related to distribution of body fat between subcutaneous and visceral fat, and (b) are racially biased, with African Americans and Hispanics showing blunted and more delayed responses than Caucasians. The omentum, the major deposit of visceral fat and macrophages in the abdomen, has been postulated to contribute to liver insulin resistance by increasing portal delivery of free fatty acids (FFAs), leading to inappropriately elevated hepatic glucose production, hyperinsulinemia, and eventually to pancreatic ß-cell failure. Another major reason behind this correlation is that visceral as compared to subcutaneous adipose tissue is a more important producer of several cytokines that are involved in the pathogenesis of insulin resistance. The ***central hypotheses*** of this application is that improvements in insulin sensitivity following bariatric surgery begin early in the postoperative period (10-30 days) and are mediated by changes in the secretion of energy-related peptides, while the long-term effects (greater than 1 month) are mediated by down-regulation of inflammatory factors. We speculate that these factors will exhibit racially biased trends and may underlie the different metabolic responses of African Americans and Hispanics versus Caucasians. .

Additionally, we hypothesize that the removal of the omentum in combination with bariatric surgery will speed up the reversal of insulin resistance state and will diminish the racial differences in response to bariatric surgery.

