**Study Day 1 is like Day 2 (clamp study day) above, except:**

- DEXA is performed this day (prior to clamp study)
- Initial labs are drawn this day

**Subject will have operation, with or without omentectomy, then repeat the above procedures 1-, 6-, 12, and 24-months later. Subjects may also be asked to repeat these procedures at 3, 4, and 5 years post-operatively.**

1. **Risks**

**List all adverse effects observed in animal studies, previous human studies, or laboratory observations. List the frequency expected for the side effects and a statement that there may be unknown or unanticipated adverse effects.**

- If subject is uncomfortable in enclosed, small spaces, the metabolic chamber may cause anxiety
- IVs may cause slight discomfort, swelling, bleeding, bruising, clotting, or infection
- In the event of an arterial line being placed, insertion of catheter may cause bleeding, bruising, nerve damage, or infection
- Rarely, the insertion of a needle into an artery or vein may cause damage to the artery or vein and a clot may develop.
- There is a small risk of low blood sugar
- Lidocaine (used for biopsies) may cause burning and/or local rash or irritation. There is also a risk of heart rhythm problems. Although rare, it is possible that lidocaine could cause a tingling feeling around the mouth, dizziness, blurred vision, drowsiness, confusion, and/or seizures.
- There is exposure to radiation (from DEXA and tritiated glucose) equivalent to 3 months of radiation from natural surroundings
- The muscle/fat biopsies may cause soreness, bruising, infection, nerve damage or a hematoma.
- Removal of the omentum may increase chances of bleeding and will increase time under anesthesia
- As with any medical treatment, there may be unknown or unforeseeable risks associated with taking part in this research study.

1. **Reporting of Adverse Events or Unanticipated Problems involving Risk to Participants or Others**

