Initial analyses will examine the short-term effects of race and surgical procedure (bariatric surgery + omentectomy), and the interaction effect of race by surgical procedure on change in measures of body composition, inflammatory factors, hormones, energy-related peptides, and health-related quality of life following bariatric surgery. The general case statistical method is mixed-model repeated measures analysis of variance with tests of: (a) the within-subjects effect of time; (b) the between-subjects main effects race and surgical procedure; and (c) race by procedure by time interaction effects. Simple contrasts will be used to test effects at postoperative week four in relation to preoperative measure. Statistical tests of main and interaction effects of race and omentectomy on any contrast are analogous to interaction of these effects with the within-subject change scores (simple contrasts). Assuming a within-subject correlation between longitudinal data points that is as low as 0.35 in the combined sample (n=132), power is adequate (85%) to detect a small effect (d=0.3) of time for any contrast. Power to detect, for any contrast, medium (f=0.30) overall main effects of race and omentectomy and the race by omentectomy interaction effect is 92%. This statistical design will also be applied within each racial group (n=66) to more explicitly examine the effect of omentectomy, and within each surgical group (n=66) to more explicitly examine the effect of race. For these analyses, the power to detect medium to large (d=0.70) effects for any contrast is 80%.

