**Table of Events**

|  | **Before Surgery**  **(GCRC)** | **Surgery** | **4 wks**  **post-op** | **6 mon**  **post-op** | **12 mon**  **post-op** | **24 mon**  **post-op** | **3, 4, 5 yrs post op** |
| --- | --- | --- | --- | --- | --- | --- | --- |
| **History and Physical/Labs** |  |  |  |  |  |  |  |
| **DXA** |  |  |  |  |  |  |  |
| **Metabolic Chamber1** |  |  |  |  |  |  |  |
| **Chamber Blood Samples2** |  |  |  |  |  |  |  |
| **24 hour Urine** |  |  |  |  |  |  |  |
| **Metabolic Studies3** |  |  |  |  |  |  |  |
| **Omentum Biopsy4** |  |  |  |  |  |  |  |
| **Muscle Biopsy** |  |  |  |  |  |  |  |
| **Subcutaneous Fat Biopsy** |  |  |  |  |  |  |  |
| **SF 36 Questionnaire** |  |  |  |  |  |  |  |

1 Only subjects enrolled to be in the metabolic chamber

2 Only subjects enrolled to be in the metabolic chamber

3 May include insulin clamp (using tritiated glucose and/or deuterated glucose), amino

acid infusion for protein kinetics, and glycerol/palmitate infusion for lipolysis and FFA

kinetics

4 Only if other abdominal operations are needed

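### The week-four power figures at n=132 do not apply to hourly peptide profiles or to DEXA, and the protocol contradicts itself on which of these are collected at month 1

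*Protocol*

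**What the plan says.** **Hypothesis and measurements.** The Rationale and Specific Aims section states that improvements in insulin sensitivity "begin early in the postoperative period (10-30 days) and are mediated by changes in the secretion of energy-related peptides". The parameter list that closes the specific aims, which applies to all three, names diurnal and food-induced secretion of adipokines and of peptides such as ghrelin and PYY. It also names regional fat by body circumferences and DEXA.

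**Chamber schedule.** The chamber heading in Study Procedures says that subjects are assigned to the chamber preoperatively and "will have chamber studies again at 6-, 12-, and 24-months post-operatively". After Study Day 2 the same group is to have the operation, "then repeat the above procedures 1-, 6-, 12, and 24-months later".

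**Hourly sampling.** Hourly samples from 0730 to 2030 appear only in the chamber group's Study Day 1. The Table of Events footnotes the chamber blood samples as "Only subjects enrolled to be in the metabolic chamber". The number of chamber subjects is not given.

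**DEXA.** The chamber list has "DEXA (except 1-month post op" as its exception. The list for subjects outside the chamber, whose visits include month 1, says "DEXA is performed this day (prior to clamp study" and makes no exception.

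**Analysis.** Statistical Considerations tests short-term effects "on change in measures of body composition, inflammatory factors, hormones, energy-related peptides" and quality of life. The contrast is week four against the preoperative value. Power is stated as 85% for time (n=132), 92% for race, omentectomy and their interaction, and 80% for d=0.70 within a racial or surgical group (n=66), each for any contrast.

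**The concern.** Four weeks is the only scheduled visit inside the early window of the central hypothesis. The mechanism proposed for that window is a change in secretion, and the protocol's measure of secretion is a diurnal and food-induced profile, which needs serial samples. Those samples come from the chamber day. The clamp day cannot replace them, because the subject is fed only at its end.

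The power statement makes no distinction between outcomes. It attaches one set of figures, at full short-term enrolment, to every contrast in a list that includes peptides and body composition. A reader would conclude that week-four secretion profiles and DEXA are tested with 80% to 92% power. The procedures do not provide that number of observations for either. A week-four profile that is not taken cannot be recovered later, so an unclear schedule could cost the data as well as misstate the power.

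**Working it through.** **1. Reproducing the stated power.** Inputs from Statistical Considerations: tests "for non-directional tests at the 0.05 alpha level"; 66 Caucasian and 66 African American or Hispanic participants, each split 33:33; negligible attrition to week four; within-subject correlation 0.35.

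- Time effect (paired t): standardised change = 0.3/√(2(1 − 0.35)) = 0.3/√1.3 = 0.263. Noncentrality = 0.263 × √132 = 3.02, df 131. Power 85.1% (stated 85%).
- Factorial effects (F, 1 and 128 df): λ = 0.30² × 132 = 11.88. Power 92.8% (stated 92%).
- Within one group (two-sample t, 33 v 33): noncentrality = 0.70 × √(33/2) = 2.84, df 64. Power 80.0% (stated 80%).

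All three reproduce. The figures are right if every one of the 132 contributes the outcome at baseline and at week four.

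**2. Who contributes what at month 1, as written.**

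| Measure | Chamber subjects | Other subjects |
|---|---|---|
| Weight, circumferences, SF-36 | Yes, by the closing sentence | Yes |
| Clamp, tracers, biopsies | Yes, by the closing sentence | Yes |
| Hourly samples | No by the heading; yes by the closing sentence | No |
| DEXA | No | Yes |

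The number with hourly profiles is therefore zero under the heading, or the chamber subset under the closing sentence. The number with week-four DEXA is 132 minus the chamber subset under either reading. Neither is 132 unless all subjects, or none, enter the chamber, and the protocol describes both groups.

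**3. Illustration of size.** The chamber number is not stated, so N below is an assumption. The formulas are those of step 1, with effects of d=0.3 (correlation 0.35) and f=0.30, and four equal cells.

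| N with week-four data | Noncentrality (time) | Power, time | λ (factorial) | Power, factorial |
|---|---|---|---|---|
| 20 | 1.18 | 20% | 1.80 | 24% |
| 40 | 1.66 | 37% | 3.60 | 46% |
| 66 | 2.14 | 56% | 5.94 | 67% |
| 100 | 2.63 | 74% | 9.00 | 84% |
| 132 | 3.02 | 85% | 11.88 | 93% |

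The same table serves DEXA with N equal to the subjects outside the chamber. If 66 of the 132 were in the chamber, 132 − 66 = 66 would have week-four DEXA, with power 56% and 67%.

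**The case against.** The strongest reply is that a month-1 chamber visit is the more natural reading. The chamber heading allows for exceptions noted elsewhere, the closing sentence includes month 1, and an instruction to skip DEXA at month 1 makes sense only if that Study Day 1 takes place. The Table of Events has a four-week column that may settle the matter, but its marks are not in the available text. This stands, and it means that zero profiles at week four is one side of a contradiction and cannot be stated as fact. It does not rescue the power claim, since the other side still gives only the chamber subset.

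A reader might go further and infer that the early hypothesis has no data. The documents do not support that. Clamp, tracer, biopsy, weight and circumference measures are listed at month 1, and a basal hormone or peptide assay is not excluded, although the laboratory list does not name one. The gap concerns the secretion profiles and DEXA.

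Two other inferences should also be avoided. DEXA is not skipped for everyone at month 1; the exception is in the chamber list only. Nor does the protocol show that the chamber group is a selected one: it says that subjects are assigned and does not say how. Omitting DEXA at four weeks may be deliberate, since the Study Plan expects minimal change in BMI or body composition then.

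Finally, the size depends on an unstated number. The Study Plan gives 150 per arm, 300 in all. A third to a half of 300 would be about 25 to 37 per cell, with a detectable within-group effect of about 0.81 to 0.66 SD, which straddles the stated 0.70. The loss could therefore be modest. The power section, however, is built on 132.

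**Conclusion.** The point holds in a limited form. The protocol contradicts itself on whether chamber studies and hourly sampling take place at month 1, and it treats month-1 DEXA differently in the two groups. The week-four power figures are correct for outcomes measured in all 132 participants. They do not apply to diurnal or food-induced profiles, or to week-four DEXA, under either reading of the schedule.

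The size cannot be fixed from the document. With 40 to 66 chamber subjects, assumed and spread equally over the four cells, power for the profile contrasts would be about 37% to 56% for time and 46% to 67% for the factorial effects, against the stated 85% and 92%. If the heading governs, there is no week-four profile contrast at all. The conclusion that n=132 is the wrong number for these outcomes needs none of these assumptions; it requires only that some subjects are in the chamber and some are not, as the protocol describes.

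**What to change.** 1. Reconcile the chamber heading, the Study Day 1 lists, the two closing sentences and the Table of Events, so that they agree on which chamber, hourly-sample and DEXA measures occur at month 1 and in whom. State the planned number of chamber subjects and how they are assigned.
2. Limit the n=132 (and n=66) power statement to outcomes measured in every participant at week four. Examples are weight, circumferences and any hormone or peptide assayed in a basal sample before the clamp. Those assays need to be named, because the laboratory list does not include them, and the Table of Events footnote saying that the metabolic studies may include a clamp should be made consistent with this.
3. Restate power for the hourly-profile and DEXA contrasts at the numbers and visits where they are actually collected.

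This is a protocol clarification and requires no new procedure; a basal peptide assay would use blood from an existing visit. The price is a less favourable stated power for the profile outcomes. The week-four peptide claim in all participants would also cover basal levels and not diurnal secretion, which is narrower than the central hypothesis. Whether DEXA at week four is kept or dropped should follow from the reconciliation and need not be settled in advance.
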